### **3.2.2 Training**

Care provider: 1 hour of initial training is provided before starting to use the device and is generally considered as sufficient for use of the device. Additional training will be provided upon request.

For the patient, there is no training required other than oral instruction at the time of use from the caregiver.

### **3.2.3 Contact with body**

The Zenicor ECG device makes skin-contact to the thumbs of the patient via the electrodes. The electrodes are made of standard medical grade AgCl-ceramic.

### **3.3 Clinical Evidence to Date**

The device has been on market since 2010. No recall has been made. Over 25 published scientific studies and 4 Doctoral theses have been made using the Zenicor device. A complete list of references can be found on the Zenicor website (<https://zenicor.com/list-of-references-2/>).

### **3.4 Medical Device: Rationale for the intended purpose in study**

The product is in regular use in over 350 clinics in Europe and has been validated in more than 25 scientific publications and four Doctoral theses.

### **3.5 Explanation for choice of comparator (or placebo)**

There will be no systematic AF screening in patients assigned to the control group. In these patients, pulse taking and ECG-recordings will be performed according to the treating physicians' clinical judgment. As a general rule, all patients hospitalized in Internal Medicine at Hospital Fribourg will have their vital signs taken at least once daily by trained nurses. Additional screening will be performed if the patient presents signs and symptoms suggestive of or consistent with AF.

This trial assesses the efficacy of a screening method. In our opinion, there is no need for a sham to control the screening method.

### **3.6 Risks / Benefits**

Guidelines strongly and uniformly recommend anticoagulation in patients with AF in order to reduce the thromboembolic risk. The benefits of oral anticoagulant therapy are directly proportional to the underlying stroke risk as measured by hypertension, age, diabetes mellitus, congestive heart failure, prior stroke, vascular disease, and gender (CHA2DS2 -VASc score). Despite the documented benefits of anticoagulation in high-risk patients, bleeding complications are a common concern with the use of anticoagulant. The factors associated with a higher bleeding risk are similar to those conferring a higher thromboembolic risk. Nevertheless, it is the patients with the highest thromboembolic risk that benefit the most from oral anticoagulant therapy.

A potential risk of the Detect-AF study is the overdiagnosis of atrial fibrillation. This might lead to a non-indicated anticoagulant treatment and might expose the patients to an unnecessarily increased bleeding risk.

However, every case of new AF diagnosed by use of the screening method will be reviewed by two independent cardiologists. In case of uncertainty, additional recordings, e.g. Holter or R-Test will be performed.

### **3.7 Justification of choice of study population**

The 2016 ESC-Guidelines for the management of atrial fibrillation underscore the importance of the

evaluation of systematic AF screening in at-risk populations. Hospitalized patients constitute such an at-risk population because of their older age and their often multiple comorbidities predisposing to AF. To our knowledge, this is the first study evaluating a systematic screening method to detect atrial fibrillation in hospitalized patients.

## **4. STUDY OBJECTIVES**

### **4.1 Overall Objective**

The aim of this study is to assess the efficacy of a one-lead ECG handheld device (Zenikor) for the detection of previously unknown atrial fibrillation (AF).

### **4.2 Primary Objective**

The primary objective is to assess the detection rate of atrial fibrillation with a one-lead ECG handheld device (Zenikor) in hospitalized patients.

### **4.3 Secondary Objectives**

Secondary objectives are to assess the impact of AF screening on clinical endpoints such as death, ischemic stroke, systemic embolism and myocardial infarction.

## **5. STUDY OUTCOMES**

### **5.1 Primary Outcome**

The primary outcome is the proportion of newly detected atrial fibrillation in percent.

### **5.2 Secondary Outcomes**

Secondary outcomes are death, cardiovascular death, stroke, transient ischemic attack or systemic embolism, myocardial infarction and bleeding at 2, 5, and 10 years after study enrollment.

## 6. STUDY DESIGN

### 6.1 General study design and justification of design

This is a single center, open label, randomized control trial (RCT) with an allocation ratio of 1:1. All patients admitted to the Internal Medicine Department of Hospital Fribourg will be screened for study enrollment. After enrollment, patients will be randomized to either the screening or the control group.

[figure not shown]

### 6.2 Methods of minimising bias

#### 6.2.1 Randomisation

Participants will be randomized 1:1 to either the screening or the control group via a computer generated randomization sequence ([www.randomizer.org](http://www.randomizer.org)).

#### 6.2.2 Blinding procedures

There is no blinding in the present study. We judge the employment of a sham-controlled screening unnecessary.

## **7. STUDY POPULATION**

### **7.1 Eligibility criteria**

All patients admitted to the Internal Medicine Department at Hospital Fribourg throughout the study period will be screened for study enrollment. Patients with known or previously documented AF, patients with a cardiac pacemaker, and implantable cardioverter-defibrillator or intra-cardiac monitoring device will be excluded from the present trial. Patients with an estimated life expectancy of < 6 months will likewise be excluded. Patients unable or unwilling to provide written-informed consent, to participate in the study procedures or in clinical follow-up will be excluded from the trial.

### **7.2 Recruitment and screening**

Study nurses will screen all patients admitted to the Internal Medicine Department at Hospital Fribourg throughout the study period for eligibility. If the eligibility criteria are met the patient will be formally enrolled. The written-informed consent form will be signed by the patient as well as by one of the participating physicians who is at the patient's disposition should the latter have any questions regarding to the trial.

### **7.3 Assignment to study groups**

Randomization will be performed using a computer generated random list of numbers. A research nurse will assign the patients to the study groups according to the previously generated randomization sequence after study enrollment.

### **7.4 Criteria for withdrawal / discontinuation of participants**

Patients can withdraw from the study at any given time and without providing any reason at all. Patients may be discontinued from the trial if they refuse to comply with the study intervention.

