|                                               | 
patients with a cardiac pacemaker, and implantable cardioverter-defibrillator or intra-cardiac monitoring device will be excluded from the present trial. Patients unable or unwilling to provide written informed consent and those unable or unwilling to participate in the study procedures or follow-up will likewise be excluded. Patients with an estimated life expectancy of <6 months will be excluded.
                                                                                                                                                                                                                                                                                                                                                                                                                                                                                                                                                                                                                                                                                                                              |
| Measurements and procedures:           | 
Patients allocated to the treatment group will undergo twice daily monitoring with the handheld Zenicor ECG. Additional recordings will be obtained whenever patients notice palpitations. Recordings will be obtained in the presence of specially trained nurses. The recordings will then be validated through a web-based interface offered by Zenicor.
 
The one-lead ECGs will be reviewed by the investigating physicians through the Web-based analysis service (Zenicor-ECG Doctor System) assessing for the presence of atrial fibrillation.
 
Patients in whom AF is newly diagnosed during the trial will undergo a prespecified work-up consisting of transthoracic echocardiography, blood analysis and risk stratification. For patients with non-valvular AF in whom oral anticoagulation is indicated according to the 2016 ESC-Guidelines, NOACs will be the treatment of choice.
 
All enrolled patients will be followed clinically at 2, 5 and 10 years to assess the occurrence of death, cardiovascular death, stroke or transient ischemic attacks, systemic embolism, myocardial infarction and bleeding.
 |

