## **2.8 Early termination of the study**

The Sponsor-Investigator (and any competent authority) may terminate the study prematurely according to certain unforeseen circumstances. These may include but are not limited to:

- ethical concerns,
- insufficient participant recruitment,
- when the safety of the participants is doubtful or at risk, respectively,
- alterations in accepted clinical practice that make the continuation of a clinical trial unwise,
- early evidence of benefit or harm of the experimental intervention

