## **8. STUDY INTERVENTION**

### **8.1 Identity of Investigational Products (treatment / medical device)**

#### **8.1.1 Experimental Intervention (treatment / medical device)**

Participants allocated to the treatment group will place their thumbs on the device twice daily and whenever they notice palpitations. Recordings will be obtained in the presence of specially trained nurses. The recordings will then be validated through a web-based interface operated by Zenicor (Zenicor-ECG Doctor System). Each one-lead ECG will be reviewed by the investigators via the Web-based analysis service (Zenicor-ECG Doctor System) to assess the presence of AF.

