#### **8.1.2 Control Intervention (standard/routine treatment / medical device)**

Patients allocated to the control group will not undergo systematic monitoring of AF. In those patients, recording of 12 lead ECG or any other monitoring modalities will be employed according to routine clinical practice.

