#### **11.3.2 Secondary Analyses**

A secondary analysis will focus on subgroups. Pre-specified subgroups comprise gender, age, diabetes, hypertension, ischemic heart disease, congestive heart disease and all subcategories of the CHADS-Vasc Score. Additional analysis will be performed on clinical follow-up. Event-free survival between the intervention and the control group will be compared at 2, 5 and 10 years according to the Kaplan-Meier method. Adjustment for eventual imbalances will be performed by using Cox

proportional hazards given that the data do not violate the proportionality assumption.

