## **11.4 Handling of missing data and drop-outs**

Missing data will be omitted pairwise from the analyses. Whenever data is missing, it will be explicitly stated in the final results of the study. Missing data arising from a loss to follow-up will be censored. The number of drop-outs will be provided in a flow-chart along with the reasons for said drop-out.

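### Section 7.4 makes refusing the recordings a ground for leaving the whole trial; in practice this can end follow-up in the screening arm only, and so can bias the telephone-collected clinical outcomes

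*Protocol*

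**What the plan says.** Section 7.4 gives two ways out of the study. Patients may withdraw at any time, which is open to both arms. In addition, "Patients may be discontinued from the trial if they refuse to comply with the study intervention". What they leave is the trial, not the recordings.

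The two arms differ in what there is to refuse. Section 8.1.1: "Participants allocated to the treatment group will place their thumbs on the device twice daily and whenever they notice palpitations". Section 8.1.2: "Patients allocated to the control group will not undergo systematic monitoring of AF"; controls receive routine practice.

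On follow-up, the synopsis says: "All enrolled patients will be followed clinically at 2, 5 and 10 years to assess the occurrence of death", and goes on to list the other clinical events. Section 5.2 makes these the secondary outcomes, ending with "myocardial infarction and bleeding at 2, 5, and 10 years after study enrollment". Section 9.2.2 has the investigator telephone patients for the secondary outcomes and takes deaths from the Swiss population register.

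On analysis, section 11.3.2 states: "Event-free survival between the intervention and the control group will be compared at 2, 5 and 10 years according to the Kaplan-Meier method". Section 11.4 adds: "Missing data arising from a loss to follow-up will be censored".

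Section 2.6 keeps the data gathered before consent is withdrawn. No section says whether a patient discontinued under 7.4 is still telephoned, still looked up in the register, or still analysed as randomised.

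**The concern.** The intervention is a short thumb recording during the hospital stay, while the clinical outcomes are collected over ten years by other means. Whether a patient goes on using the device has no bearing on whether that patient can be telephoned or found in a register. Section 7.4 nevertheless ties the two together.

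The tie works on one arm. A control patient has no in-hospital study procedure to refuse, so discontinuation for refusal can in practice remove screening patients only. Censoring these patients gives a fair comparison only if their later risk equals that of the patients who remain, and nothing in the protocol supports that assumption for inpatients who decline a recording. At stake is the secondary objective, the effect of screening on clinical events. The primary outcome, AF detection, is not the subject of this point.

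An analysis plan could define who is analysed and how, but it could not recover events that were never collected. The rule therefore has to be right in the protocol.

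**Working it through.** **Passages side by side.** Under 7.4 a screening patient who declines recordings can be taken out of the trial. Under the synopsis every enrolled patient is followed at 2, 5 and 10 years. For a patient discontinued under 7.4 with no further contact, both cannot hold, and no section says which prevails.

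**The plan's own figures.** Section 11.2 requires 745 per group and enrols 800. The margin is 800 − 745 = 55, and 55/800 = 6.875%; the reverse check is 745/(1 − 0.06875) = 800. Power at 745 per group for 3% against 1%, two-sided 5%, is 78.8% by the normal approximation, close to the stated 80%. The sample size is not affected by this point. The 55 serves below only as an upper bound on refusals.

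**Inputs that the protocol does not give (assumptions).** The share *d* of the screening arm discontinued for refusal; the event-risk ratio *k* of refusers to compliers; and the ten-year risk *r* of a telephone-collected event, set at 30% in both arms, with no true effect of screening.

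**Formula.** The whole screening arm has risk *r*, made up of compliers at risk *c* and refusers at risk *kc*:

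(1 − d)·c + d·k·c = r, so c = r / (1 − d + d·k).

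Refusers would leave during the hospital stay and add almost no follow-up time, so the retained screening arm shows about *c* while the control arm shows *r*.

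**Results with r = 30%.**

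| d | k | calculation | screening arm shows | difference from 30.0% |
|---|---|---|---|---|
| 2% | 0.5 | 0.30/0.990 | 30.3% | +0.3 points |
| 2% | 1 | 0.30/1.000 | 30.0% | 0 |
| 2% | 1.5 | 0.30/1.010 | 29.7% | −0.3 points |
| 6.875% | 0.5 | 0.30/0.965625 | 31.1% | +1.1 points |
| 6.875% | 1 | 0.30/1.000 | 30.0% | 0 |
| 6.875% | 1.5 | 0.30/1.034375 | 29.0% | −1.0 point |
| 6.875% | 2 | 0.30/1.06875 | 28.1% | −1.9 points |

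The spurious risk ratio, c/r = 1/(1 − d + d·k), does not depend on *r*. It is 0.99 for 2% at 1.5 times the risk, and 0.97 and 0.94 for 6.875% at 1.5 and 2 times. If refusers stay in follow-up, d = 0 for this route and the ratio is 1.00 whatever the value of *k*.

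**Scale against random error.** At 30% in groups of 745 and 800, the 95% half-width of the difference is 1.96 × √[0.30 × 0.70 × (1/745 + 1/800)] = 4.6 points.

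**The case against.** The strongest reply is that 7.4 is permissive: patients may be discontinued, and the sentence does not say in terms that the calls stop. Section 7.1 also excludes, before randomisation, patients unwilling to take part in study procedures or follow-up, so refusal of a 30-second recording should be uncommon. Both points stand. They make the loss less likely; they do not settle what happens when the rule is used. Section 11.2 itself expects drop-outs after inclusion.

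Deaths come from a register that needs no telephone call. This stands as far as it goes: all-cause death is less exposed, if the look-up continues for discontinued patients. The illustration should therefore be read for telephone-collected events.

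The upper case attributes all 55 patients to refusal, whereas section 11.2 sets that margin for ineffective measurements and other losses too. It is a ceiling, not an expectation. Even its largest artefact, 1.9 points, lies well inside the 4.6-point random error. Some refusers would also decline calls, and no rewording would recover them.

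A reader might go further in three ways that the protocol does not support:
- That the rule does bias the results in favour of screening. The protocol says nothing about who refuses; refusers could be well patients who see no need, which would reverse the sign.
- That the artefact matches or exceeds the true effect. The planned 3% against 1% means (0.03 − 0.01) × 800 = 16 extra detections, at most 2 points if each spared a patient an event. Both artefacts, 1.0 and 1.9, are below that ceiling, and the protocol gives no basis for estimating the actual effect.
- That section 2.8 has the same fault, because it lists "early evidence of benefit or harm of the experimental intervention" as a reason to end the study. That clause is also permissive, does not say that follow-up stops, and is a separate matter.

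**Conclusion.** The point holds in a limited form. Section 7.4 merges stopping the recordings with leaving the study. Its refusal clause can in practice apply to one arm only, and it is inconsistent with the synopsis commitment to follow all enrolled patients. Combined with censoring, its use can bias the between-arm comparison of stroke, TIA, embolism, infarction and bleeding. This requires both that the rule is applied and that refusers differ in risk from compliers.

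The size is unknown. Under the assumed 30% risk and no true effect, it ranges from about 0.3 points (2% refusal, 1.5 times the risk) to 1.0 to 1.9 points in the upper case of 6.9%; it is zero at equal risk and of opposite sign if refusers are at lower risk. Because the rule decides whether outcomes are collected at all, it is more than a detail that can wait for the analysis plan.

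**What to change.** Amend section 7.4 to separate the two events. A patient who refuses recordings stops the recordings only, stays in the randomised arm, and remains in telephone and register follow-up at 2, 5 and 10 years. Follow-up ends only when the patient explicitly withdraws consent to it, with the date and scope recorded (recordings, calls, register look-up). Remove discontinuation from the trial as a consequence of refusing the intervention.

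Reconcile 7.4 with the synopsis and with section 9.2.2, stating there that the register is consulted for patients who stopped recordings unless they withdrew from that as well.

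The cost is a wording amendment and telephone calls that the synopsis already promises for these patients. The change concerns data collection only and leaves the sample size as it is.

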## **8. STUDY INTERVENTION**

### **8.1 Identity of Investigational Products (treatment / medical device)**

#### **8.1.1 Experimental Intervention (treatment / medical device)**

Participants allocated to the treatment group will place their thumbs on the device twice daily and whenever they notice palpitations. Recordings will be obtained in the presence of specially trained nurses. The recordings will then be validated through a web-based interface operated by Zenicor (Zenicor-ECG Doctor System). Each one-lead ECG will be reviewed by the investigators via the Web-based analysis service (Zenicor-ECG Doctor System) to assess the presence of AF.

#### **8.1.2 Control Intervention (standard/routine treatment / medical device)**

Patients allocated to the control group will not undergo systematic monitoring of AF. In those patients, recording of 12 lead ECG or any other monitoring modalities will be employed according to routine clinical practice.

#### **8.1.3 Packaging, Labelling and Supply (re-supply)**

The Zenicor-ECG is delivered with free carrier on site at the time of the education. Each device is labelled with a unique serial number, example A002130.

### **8.2 Medical Device Accountability**

During the trial period Zenicor is accountable for any damage to the devices. Broken or damaged device will be sent to Zenicor for service or destruction. A replacement device will be sent to the customer during the service period or as replacement for the broken/lost device.

### **8.3 Return or Destruction of Medical Device**

Devices can be returned by mail in a padded box to Zenicor after the study or purchased for further use in the clinic.

## 9. STUDY ASSESSMENTS

### 9.1 Study flow chart(s)/table of study procedures and assessments

|                                                                                | Patient information and inclusion | Intervention Period                      | Investigations                      | Follow-up                          |
|--------------------------------------------------------------------------------|------------------------------------------------------|-------------------------------------------------|--------------------------------------------|-------------------------------------------|
| Visit                                                                   | Once or twice                                 | twice daily                              | In patients with newly diagnosed AF | 2 years,
5 years,
10 years |
| Time                                                                    | 20 minutes                                    | 30 seconds
twice daily (or
more) | 30 minutes                          |                                           |
| Patient information                                                     | x                                                    |                                                 |                                            |                                           |
| Informed Consent                                                        | x                                                    |                                                 |                                            |                                           |
| Baseline characteristics:
age, gender,
CHAD-VASC
score etc. | x                                                    |                                                 |                                            |                                           |
| Randomisation                                                           | x                                                    |                                                 |                                            |                                           |
| ECG recordings                                                          |                                                      | x                                               |                                            |                                           |
| Primary outcome                                                         |                                                      | x                                               |                                            |                                           |
| Laboratory tests:
TSH ,lipid profile
etc.                       |                                                      |                                                 | x                                          |                                           |
| ECG, Echo                                                               |                                                      |                                                 | x                                          |                                           |
| Secondary outcome (clinical follow-up)                                  |                                                      |                                                 |                                            | x                                         |

 A period of 24 hours of reflection will be granted to the patient for the constant process

